#### Moderation analysis

In addition, when employing mobile interventions, it may appear relevant to investigate whether users’ technical experience moderates the intervention’s effect. For this reason, participants’ user experience will be considered as a moderator. To detect significant moderation, the Johnson-Neyman (J-N) [120, 121] procedure will be used to pinpoint at which moderation value a meaningful difference between groups is observable in the primary outcome.

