#### Explorative hypotheses

In addition, two explorative analyses will be conducted to investigate a potential underlying mechanism and further possible modifier of the assumed effect.

More specifically, given that levels of recreational activities are of major importance for the recovery process, they may account for the intervention’s underlying mechanism. For instance, in one intervention study, recreational activities appeared to mediate the intervention’s effect, with workers who engaged in recreational activities during lunch breaks experiencing higher levels of wellbeing at the end of their work day [43]. These findings are in line with those of an earlier RCT, in which the intervention’s effect also was mediated by increased recreational activities, leading to fewer sleep complaints [60]. In accordance with these findings and Holidaily’s intention to foster recreational activities, activity levels may explain, to a certain degree, the mechanism through which the intervention works, if it works at all.

Moreover, participants user experience might determine participants engagement [71, 72], where in turn, participants engagement may determine interventions efficacy [73, 74]. Recent findings by this study team suggest that users’ recovery is uniquely predicted by user experience [58]. On an explorative basis, we therefore intend to investigate whether users’ experience moderates the intervention’s effect.

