#### Analysis of secondary outcomes and other variables

Secondary health-related outcomes will also be compared in the intervention and waitlist-control groups. It is important to note that all analyses related to secondary outcomes will be descriptive and non-explanatory in nature. As intervention research on promoting recovery after vacations is in its infancy, evaluating a wide range of secondary outcomes will help us gain knowledge to generate further hypotheses and guide future studies. Finally, all variables not directly related to health, like personal and work characteristics, are considered other variables. Other variables will be used to evaluate a potentially underlying mechanism, effect modifier and confounders of the primary study outcome. Moreover, app-use compliance will be tracked and analysed on a descriptive basis (i.e., how often was the app used).

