#### Sample size calculation

Sample size calculation was based on the expected standardized difference in the primary outcome measure — work-related rumination (Irritation Scale, [76]) — between the intervention and control groups 2 weeks post vacation. Evidence from meta-analyses and systematic reviews on the efficacy of digital interventions for mental health, and specifically stress management, in workers indicate an effect size of ﻿*g* = 0.54 [77]. More precisely, data on mental health apps as a standalone treatment for clinical samples targeting various conditions yield mixed results: for instance, a significant effect for depression ﻿*g* = 0.33, but no effect for ﻿anxiety [70]. Few RCTs indicate the potential of any app-based intervention targeting stress-related complaints amongst workers [65, 66, 74]. Though clear results concerning the efficacy of app-based interventions cannot be drawn, findings nonetheless indicate their potential. From a public health perspective, the aim is to reach the whole population. As such, smaller effects are meaningful, as more people can potentially benefit from an intervention. Taking these two lines of reasoning together, we regard an effect of *d =* 0.20 for work-related rumination as meaningful, especially when considering that the app constitutes a low-intensity self-help intervention for the general working population. A priori G*Power analysis [78] for a two-tailed test, in which 80% power and a 5% significance level are assumed, indicates that an overall sample size of *N* = 788 is needed to detect differences statistically.

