Fifth, exploring whether users’ technical experience with Holidaily contribute to a greater intervention effect could be of great value when designing future app-based interventions. For this reason, moderation analysis will be performed, focusing on Holidaily users’ experiences and the intervention’s effectiveness.

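### The moderation analysis detects moderation by Johnson-Neyman regions, which test whether the arms differ at a given moderator value, not whether the effect changes with the moderator

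*Protocol article*

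**What the plan says.** The Explorative hypotheses section sets the question: "On an explorative basis, we therefore intend to investigate whether users’ experience moderates the intervention’s effect". The Moderation analysis section names user experience as the moderator and gives the decision rule: "To detect significant moderation, the Johnson-Neyman (J-N) [120, 121] procedure will be used to pinpoint at which moderation value a meaningful difference between groups is" visible on work-related rumination. It mentions no interaction term, interaction test or confidence interval. The Mediation analysis section just before it does give a significance rule: the 95% confidence interval of the indirect effect must exclude zero.

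Other variables may also be examined as effect modifiers: "Other variables will be used to evaluate a potentially underlying mechanism, effect modifier and confounders of the primary study outcome". No method is given for them. The Study contributions section says what the moderation result is for: "exploring whether users’ technical experience with Holidaily contribute to a greater intervention effect could be of great value when designing future app-based interventions".

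Table 1 lists user experience (AttrakDiff2) at T5 and T6 only, and T6 is collected in the intervention group only. The Study design section gives controls access to the app only after they complete the T5 questionnaire.

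**The concern.** Take the model Y = b0 + b1·G + b2·M + b3·G·M + error, with G the arm and M the moderator. Whether M moderates the effect is a question about b3, with null hypothesis b3 = 0. At each value m, the Johnson-Neyman procedure tests b1 + b3·m = 0, that is, no difference between arms at that value. These are different hypotheses.

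Suppose every participant gains equally (b1 not zero, b3 = 0). The confidence band for the conditional effect is narrowest near the moderator mean and widens towards the ends. The procedure then tends to show a significant region in the middle and non-significant regions outside it, although nothing is moderated. A finding reached by this rule would largely restate whether the app has an effect at all, yet it could be read as guidance on app design.

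**Working it through.** **Inputs from the protocol article**
- Effect size: "we regard an effect of *d =* 0.20 for work-related rumination as meaningful".
- Design: "A priori G*Power analysis [78] for a two-tailed test, in which 80% power and a 5% significance level are assumed", with 1:1 allocation.
- Total: "indicates that an overall sample size of *N* = 788 is needed to detect differences statistically", so 394 per arm.
- Two-tailed significance level of 0.05 for all reported p values (Statistical analyses section).

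**Assumptions, because the article gives no figure**
- Baseline-outcome correlation r from 0 to 0.5. The article plans baseline adjustment for the primary ANCOVA and does not mention it for the moderation model.
- Attrition from 0 to 30%.
- A moderator with values in both arms, unrelated to the treatment effect.

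**Step 1: reproduce the planned size.** The normal approximation gives 393 per arm (786). The exact noncentral-t calculation gives 394 per arm, 788 in total, with power 0.8006. The planned figure is reproduced.

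**Step 2: probability of a Johnson-Neyman region when b3 = 0.** The largest value over all m of (b1 + b3·m)² / Var(b1 + b3·m) equals the joint two-degree-of-freedom Wald statistic for (b1, b3). A region therefore exists when a 2-df statistic exceeds the 1-df critical value 1.96² = 3.84. With a uniform effect d, that statistic is approximately noncentral chi-square with 2 df and noncentrality

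ncp = (N/4)·d² / (1 − r²).

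- N = 788, d = 0.20, r = 0: ncp = 197 × 0.04 = 7.88, probability 85.7%.
- N = 788, r = 0.5: ncp = 7.88 / 0.75 = 10.51, probability 93.1%.
- N = 552 (30% attrition), r = 0: ncp = 138 × 0.04 = 5.52, probability 73.6%.
- No treatment effect: ncp = 0, probability exp(−3.84/2) = 14.7%.

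| Analysed N (attrition) | r = 0 | r = 0.3 | r = 0.5 |
|---|---|---|---|
| 788 (0%) | 85.7% | 88.4% | 93.1% |
| 709 (10%) | 82.4% | 85.3% | 90.7% |
| 630 (20%) | 78.3% | 81.6% | 87.6% |
| 552 (30%) | 73.6% | 77.0% | 83.6% |

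**Step 3: simulation check** (5,000 trials per scenario, N = 788, d = 0.20, b3 = 0). At r = 0 a region appeared in 84.8% of trials with a normal moderator and 85.9% with a uniform one. At r = 0.5 the figures were 93.3% and 93.7%. The interaction test rejected in 4.7% to 5.5%.

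**Step 4: a stricter reading.** Suppose moderation is claimed only if a boundary between significant and non-significant values lies inside a given moderator range. At r = 0 the rate is 83% to 85% over the observed range and about 81% between the 5th and 95th percentiles. Within ±1 SD of the mean it is about 60% at r = 0 and 54% at r = 0.5.

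**Step 5: power of the interaction test** (N = 788, r = 0.5, moderator in SD units). SE(b3) = √(4 × 0.75 / 788) = 0.0617. For b3 = 0.10, 0.10/0.0617 = 1.62 and power is about 37%. For b3 = 0.20, the ratio is 3.24 and power is about 90%.

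**The case against.** - **The wording may mean less than it says.** Pinpointing a moderator value is the language of probing. The boundaries come from a model that already contains the interaction term, so its coefficient would be estimated anyway, and the article does not rule out testing it first. This stands against any claim that a uniform effect will be reported as moderation. It does not remove the point, because the sentence makes the procedure the means of detecting significant moderation, which is a stated criterion and not a detail left to an analysis plan.
- **The calculated scenario cannot arise for user experience.** Controls have not used the app at T5, so a group-by-user-experience model cannot be fitted as described. This stands. The rates apply only to a moderator observed in both arms, and the fix must deal with user experience separately.
- **Other effect modifiers.** A reader might infer that the same rule governs the other variables. The article names no method for them, so this is not supported.
- **Size.** A reader might infer a false-moderation rate of about nine in ten. On the planning inputs it is about 86%. Reaching 90% without attrition needs a baseline-outcome correlation of about 0.4, which the article does not give, and attrition lowers the rate.
- **Importance.** The analysis is labelled exploratory, and the Limitations section confines strong conclusions to the primary outcome. This stands and limits the consequence.

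**Conclusion.** The criterion is misstated. It tests for an arm difference at particular moderator values, while the question is whether the effect varies. Taken literally, with a moderator available in both arms and any significant region counted as moderation, a uniform effect of the planned size would meet it in about 86% of trials, and in roughly 74% to 93% over the assumed attrition and correlation. An interaction test would do so in 5%. Requiring a boundary within ±1 SD lowers the rate to 54-60%, still far above 5%.

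The documents do not show that false moderation will be reported, since an interaction test might come first. The primary endpoint, sample size and primary ANCOVA are untouched. The point is worth correcting because the article intends the result to inform later app design.

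**What to change.** In the Moderation analysis section, replace the detection rule with wording to this effect: moderation is judged by the two-sided test at the 0.05 level and the 95% confidence interval of the group-by-moderator interaction in the baseline-adjusted ANCOVA; Johnson-Neyman regions are shown only to describe an interaction so established and are not themselves evidence of moderation.

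Apply this only to moderators observed in both arms, preferably measured at T1. Report user experience as an association with the outcome within the intervention group, not as moderation of the treatment effect. If other variables are examined as effect modifiers, use the same interaction rule.

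The cost is a few sentences and no new data. The downside is fewer moderation claims, because power for weak moderation is limited: about 37% for a change in effect of 0.10 SD per SD of the moderator, against about 90% for 0.20, at an assumed correlation of 0.5 and no attrition.

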## Methods

### Study design

For a proof of concept study and employing a pre-post-design, our research team has investigated the feasibility of use of the app-based intervention “Holidaily 1.0.” amongst workers (*N* = 77) [58]. Holidaily is a low-intensity, gamified, smartphone-based intervention. The app provides users with three suggestions promoting recovery behaviour daily. In this study, the intervention was begun 2 weeks prior to each worker’s vacation and continued beyond their return to daily working life. Initial findings were promising, as workers reported a significant improvement from 2 weeks before to 2 weeks after their vacation, and exhibited reduced work-related rumination during their leisure time, with an effect size of *d* = 0.68. To date, research indicates that, with no intervention, mental health variables resume baseline scores within 2 weeks after a vacation has ended [47]. Our next step is to establish whether meaningful effects can also be detected when an intervention and control group are compared.

Therefore, the current two-armed randomised controlled trial is being conducted to evaluate the efficacy of the app-based intervention “Holidaily 2.0” relative to a waitlist-control group (CG). All participants are invited via email to complete online questionnaires 2 weeks prior to their vacation, on their last working day, in the middle of their vacation, at the end of their first day working post-vacation, and 2 weeks after their vacation has ended (see Table 1). The intervention group receives an additional questionnaire 4 weeks after their vacation (extended follow-up). On average, these assessments last 15–30 min each. After the CG complete their final questionnaire, 2 weeks after their vacation, they receive an automated code via Email which allows them to immediately access Holidaily.

**Table 1 Tab1:** Overview of variables and measuring time points

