**Potential mediator and moderator**						
Mediator						
Health behaviour						
*Recreational activities (REAQ)*	✔				✔	✔
Moderator						
Technical aspects						
*User experience (AttrakDiff2)*					✔	✔

^a^ only intervention group

All procedures were approved by the ethics committee of Leuphana University in Lueneburg (reference number: 201606, EB-Antrag [name]201606_holidaily). The trial is registered with the German Clinical Trial Register (DRKS00013650).

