#### Waitlist-control group

Participants in the waitlist-control group (CG) are invited to answer the same questionnaires following the same timeframe as the IG. However, subjects in the CG only receives access to Holidaily 2 weeks after they have returned to work. Controls can, therefore, use Holidaily during their subsequent daily working life and next vacation.

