#### Moderator

##### Technical aspects: User experience.

Participants’ digital experiences using Holidaily are assessed employing a 28-item questionnaire from the AttrakDiff2 [112]. A seven-point Likert scale is used for responses. The questionnaire provides information concerning global attractiveness (ATT), pragmatic quality (PQ), hedonic quality-identity (HQ-I), and hedonic quality-stimulation (HQ-S), and has an internal consistency of ﻿*α* = 0.94 [58].

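### The explorative moderation analysis seeks the user-experience values at which the arms differ, but controls cannot have a valid user-experience score at the primary endpoint

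*Protocol article*

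**What the plan says.** All references are to the protocol article.

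- **Moderation analysis:** participants' "user experience will be considered as a moderator", and the Johnson-Neyman procedure is to "pinpoint at which moderation value a meaningful difference between groups is observable in the primary outcome".
- **Moderator, Technical aspects: User experience:** the construct is specific to this app. Participants' "digital experiences using Holidaily are assessed employing a 28-item questionnaire from the AttrakDiff2".
- **Table 1:** the row "User experience (AttrakDiff2") is ticked at T5 (two weeks post-vacation) and T6 (four weeks post-vacation) and at no earlier visit. The footnote to T6 reads "only intervention group". The T5 tick carries no such footnote.
- **Study design:** "After the CG complete their final questionnaire, 2 weeks after their vacation, they receive an automated code via Email".
- **Waitlist-control group:** "subjects in the CG only receives access to Holidaily 2 weeks after they have returned to work". The same section says that controls "are invited to answer the same questionnaires following the same timeframe as the IG".
- **Primary analysis:** the endpoint is the difference between the arms in work-related rumination at T5, analysed by ANCOVA with the baseline score as covariate.
- **Explorative hypotheses** and the abstract describe the moderation analysis as explorative.

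**The concern.** A Johnson-Neyman region is the set of moderator values at which the difference between arms is significant. It is derived from a group-by-moderator interaction, and therefore from the slope of the outcome on the moderator in each arm. Here the moderator is a rating of an app that one arm has not been given when the rating and the outcome are collected. A control slope on experience of using Holidaily is undefined.

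What is at stake is an interpretation. The abstract and the Study contributions section present this analysis as helping to explain the app's effect and to inform the design of later apps. An association within the intervention group between liking the app and ruminating less could be reported as evidence that the app works better for people with a better user experience. The design cannot show that.

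**Working it through.** **1. The plan's own figure.** The Sample size calculation section gives d = 0.20, two-sided 5%, 80% power and N = 788. The normal approximation gives n per arm = 2 × (1.960 + 0.842)² / 0.20² ≈ 393. The exact noncentral-t calculation gives 394 per arm (power 0.8006; 393 per arm gives 0.7996), so 2 × 394 = 788 is reproduced. The moderation analysis plays no part in this number.

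**2. Does a control value exist at T5?** The access rules and the visit table, side by side:

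| Visit | AttrakDiff2 in Table 1 | Controls have had study access to the app? |
|---|---|---|
| T1 to T4 | not taken | no |
| T5 (primary endpoint) | taken | no; the code is sent after this questionnaire |
| T6 | taken, intervention group only | not assessed |

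At no scheduled visit can a control participant rate their use of Holidaily.

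**3. What the interaction model can estimate.** Let Y be T5 rumination, B baseline rumination, G group (1 = intervention) and U user experience:

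Y = a + γB + τG + βU + δ(G×U) + error.

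This model has five parameters. The rank of its design matrix was checked with 394 per arm and simulated covariates.

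- *Control U missing, complete cases:* only the 394 intervention rows remain. There G equals the intercept column and G×U equals U. Rank 3 of 5; neither τ nor δ is estimable.
- *Control U set to a constant c:* then U = c − cG + G×U, an exact linear dependence. Rank 4 of 5 for c = 0, 1 and 4; β and δ cannot be separated.
- *Genuine U in both arms:* rank 5 of 5, but this design cannot supply it.

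**4. What the intervention group alone shows.** Within that arm the slope on U is β + δ. If U merely predicts rumination (β ≠ 0) with no effect modification (δ = 0), the slope is still non-zero. A fit that forces the control slope to zero reports all of β as moderation. In an illustrative simulation (assumed prognostic correlation −0.3, constant effect d = 0.20, no true moderation), all 2,000 runs declared moderation. That rate follows from the assumed correlation and the forced slope. It illustrates the mechanism and is not an estimate of size for this trial.

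**5. Timing.** U at T5 is collected after randomisation and together with the outcome. People who feel better may rate the app better, so even the within-arm slope has no clear direction.

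**6. The replacement.** Regressing Y on B and U in the intervention group has rank 3 of 3. By Fisher's z, the detectable correlation at 80% power and two-sided 5% is tanh[(1.960 + 0.842)/√(n − 3)]. With n = 394 (no dropout) this is tanh(2.802/19.77) = 0.14. The protocol gives no dropout rate. If, as an assumption, half were lost (n = 197), it would be tanh(2.802/13.93) = 0.20.

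**The case against.** **The analysis is explorative.** This stands and limits the severity. The abstract and the Explorative hypotheses section say so, and the Limitations section reserves strong conclusions for the primary outcome. The primary, sensitivity, secondary and mediation analyses are not described as using AttrakDiff2. A reader might infer that the efficacy result is compromised; nothing in the protocol supports that.

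**Controls may be given AttrakDiff2 at T5.** Table 1 does not restrict the T5 tick, and controls are said to receive the same questionnaires. A reader might infer that the score is structurally missing in all 394 planned controls and that the interaction has no data. The document does not establish this. If controls answer the items, a program will return an interaction estimate, and the defect is invalid measurement rather than missing data. The conclusion is unchanged, because people without study access to the app cannot report their experience of using it.

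**The moderator might mean general technical experience.** The Moderation analysis section does use such wording, and a general trait could exist in both arms. But the only instrument named is AttrakDiff2, defined as experience of using Holidaily, and it has no baseline assessment.

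**The analysis plan could settle the details.** A plan can add detail, but here the protocol itself fixes the instrument, its timing, the procedure and the between-group contrast, and these are incompatible.

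**Multiple imputation.** The protocol names it only in general terms. A reader might infer that user-experience scores will be invented for controls; the text does not say so. Imputation would not rescue the analysis, since no control data inform the relation between this score and the outcome.

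**Conclusion.** The moderation analysis is wrong as written: it cannot identify the user-experience values at which the arms differ in T5 rumination. With control scores missing or constant, the interaction is not estimable (rank 3 or 4 of 5). With control answers collected at T5, it is computable but not interpretable, because those answers do not measure the stated construct. In both cases only the intervention-group slope is meaningful, and it mixes prognosis, effect modification and reverse influence of the outcome on the rating.

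This rests on the access rules being followed, so that controls have not used Holidaily before T5, and on AttrakDiff2 being the moderator as defined. It does not depend on the simulation or on any dropout rate. Severity is moderate: one explorative analysis is affected, and the primary ANCOVA and N = 788 stand.

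**What to change.** 1. In the Moderation analysis section, delete the between-group Johnson-Neyman analysis. Stop calling AttrakDiff2 a moderator there, in Table 1, and where the analysis is announced (abstract, Explorative hypotheses, Study contributions).
2. Replace it with a regression of T5 rumination on the T5 AttrakDiff2 score, adjusted for T1 rumination, in the intervention group only. Report it as an exploratory association that does not show effect modification, and state that score and outcome are concurrent.
3. Mark AttrakDiff2 as intervention group only at T5 in Table 1. Do not impute it in controls, and do not analyse any control answers already collected.
4. If a true moderation question is wanted, use a variable measured at T1 in both arms. Table 1 lists several T1 measures, but none of them is user experience with the app.

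The cost is a change of wording and a table footnote; the sample size and primary analysis do not change. The price is that one exploratory claim becomes weaker: the trial can say whether users who rate the app better also ruminate less, but not that user experience changes the app's effect.
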